### Intervention

The intervention will be introduced to the mother following allocation into the massage group. The massage paradigm is modified from the preterm massage protocol of Field et al. [89] that consists of 2 parts, a tactile phase and a kinaesthetic phase. Mothers will be taught the techniques and encouraged to massage their babies for 15 min, twice a day until term equivalent age. Those allocated to the control group will receive care as usual.

Mothers will be given the following instructions both in demonstration and in written form for later reference. The tactile phase will begin with asking “baby’s permission”, in the prone position and enclosing the infant with cupped hands in a “resting hands” position (Fig. 1). A small amount of massage oil (cold-pressed fruit or vegetable oil) will be used. Maintaining a “resting hand” to the back, the mother will slowly stroke the baby with the palm of her other hand with a gentle but firm, rhythmic motion, following this sequence: head to the neck (6 times), shoulder to the hand (6 times) left and right, neck to the back to the bottom (6 times), bottom to the feet (6 times) left and right. After returning to “resting hands” position for up to a minute, this sequence will be repeated. During the massage the mother is to breathe deeply and slowly, keeping herself relaxed whilst paying attention to the baby’s stress cues which include crying, skin mottling, hiccups, gagging, apnoea and bradycardia. If signs of stress are evident, the mother will to return to “resting hands” until the baby settles and is ready for further massage. If the baby doesn’t settle, the mother will stop and re-attempt the massage later.

**Fig. 1 Fig1:**
[figure not shown]
"Resting hands" prone position in massage protocol

For the kinaesthetic phase, the baby is placed in the supine position. Again, the mother will place her palms on the baby’s body to embrace the chest in a “resting hands” position. If the baby’s eyes are open, eye contact and verbal interaction will be encouraged. Kinaesthetic stimulation will follow this sequence: 6 flexions and extensions of the right upper limb, 6 flexions and extensions of the left upper limb, 6 flexions and extensions of the right and left upper limbs together, 6 flexions and extensions of the right lower limb, 6 flexions and extensions of the left lower limb, 6 flexions and extensions of the right and left lower limbs together. After returning to “resting hands” position for up to a minute, this concludes the session. The massage sequence will be taught to the mother by the same paediatric physiotherapist trained in the Field method of massage [89].

The mothers will be provided with a structured diary to keep a record of the number and duration of each session. Massage sessions will be preferably performed around 60 min before feeding and at least 2 h after the completion of the previous session. Up to three individual teaching sessions will be given to each mother and support will be continued until the mother is considered to be competent and confident. Regular contact with the mother will ensure that she continues to use the outlined protocol. When the baby is discharged home, the mother will be asked to continue daily massages until TEA.

Infants of the CAU group will undergo routine nursery care and there will be no specific interventions. Intervention and CAU mothers will be assigned to different nursery rooms to prevent contamination. In addition, nursery staff will be briefed on the importance of maintaining the study protocol. Very close monitoring of the data collection process will ensure protocol violations will be identified and action will be undertaken to prevent this, in a sensitive manner.

#### Term participants

A term born reference group will be recruited from the postnatal wards or via interested parents for comparison to a normal infant population.

The term born reference group will be born between 37 and 41 weeks gestation following an uncomplicated pregnancy and delivery, have a birthweight > 10^th^ centile and have not required special care admission.

### Measures

#### Baseline measures

Demographics: Medical risk factors for outcome using standardised Australian and New Zealand Neonatal Network (ANZNN) data definitions [90] (e.g. gestational age, birthweight) will be collected from the baby’s case notes as baseline demographics.Prechtl’s Qualitative Assessment of General Movement [45]: Video of the baby’s general movements will be collected for general movements assessment performed at a later date by a certified assessor who will be blind to group allocation.Hammersmith Neonatal Neurological Examination (HNNE): The HNNE is a discriminative and predictive scale for the neurological examination of the preterm and term newborn [91–93]. It is derived from a combination and adaptation of items taken from Prechtl, Saint Anne Dargassies and Brazelton methods in a simplified and easy to administer protocol [92]. When compared to term born infants, preterm infants at term equivalent age have lower scores when assessed with HNNE [92]. The examination will be performed by a Paediatric Neurologist, Paediatric Physiotherapist or Neonatologist who will score the infant at the same time.Depression Anxiety Stress Scales (DASS): This self-report measure consists of three 14-item scales assessing depression, anxiety and stress over the past week. Each item has 4 response options ranging from 0 (“Did not apply to me at all”) to 3 (“Applied to me most of the time”) [94]. If questionnaire scores indicate significant emotional stress, psychosocial support will be offered. Mothers will be asked to complete this assessment.Edinburgh Postnatal Depression Scale (EPDS): The EPDS is a 10-item self-administered questionnaire developed for screening postpartum depression in women in outpatient or home visiting settings [95]. Psychosocial support will be offered and appropriate referrals made if the EPDS score is greater than 9. Mothers will be asked to complete this assessment.Mother-to-Infant Bonding Scale (MIBS): The MIBS is designed for use from day one postpartum, offering the mother one-word descriptors of possible emotions towards her new child. It is quick and easy to use and has reasonable reliability (α score 0.71) [96]. Mothers will be asked to complete this assessment.Infant Observations: These are conducted on mother-infant pairs, each of 1 h duration by one Psychoanalytic Psychotherapist trained in the Esther Bick Tavistock model of observation [85]. Each observation will be assessed using the following criteria: amount of touching by the mother, amount of visual checking if the mother is away from the infant or if the infant is asleep, amount of auditory checking, amount of talking about the infant by the mother, the infant's desire for contact with the mother, visual/physical reaching, anxiety apparent in the relationship, reports of illness or difficulties, willingness to let the observer see the infant. This will be the first of four such observations to evaluate the evolving mother-infant relationship.

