### Aim

The broad aim is to investigate the potential effects of infant massage performed by the mother, in VPT infants born between 28 and 32 weeks and 6 days gestational age. Effects on the infant will be assessed at the electrophysiological, neuroradiological and clinical levels at term equivalent age and 24 months corrected age. In addition, the impact of infant massage implemented by the mother on maternal mood and anxiety and infant attachment will be measured at term equivalent age, 12 months corrected and 24 months corrected age.

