### Hypothesis

The primary hypothesis to be tested is that infant massage by the mother in VPT infants promotes favourable processes in brain development, which can be functionally measured with dense array electroencephalography (dEEG).

Secondary hypotheses to be tested include the following:Infant massage by the mother in VPT infants promotes favourable processes in brain development, which can be detected structurally at term equivalent age, and functionally at term equivalent age and 24 months corrected age.Infant massage by the mother in VPT infants reduces maternal depression, anxiety and stress associated with preterm birth.Infant massage by the mother in VPT infants enhances infant attachment.

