### Secondary outcomes

i.Other EEG parameters at term equivalent age (TEA)Global power in delta, theta and alpha bands, absolute and relative power for each frequency band, interhemispheric coherence and partial directed coherence will be analysed.ii.MRI measures at TEAA brain MRI will be performed using a 3.0-T (Siemens TIM Trio, Erlangen, Germany) and an MRI-compatible incubator with a dedicated head coil (LMT Lammers Medical Technology, Lubeck, Germany). The infants will be fed, fitted with earmuffs to minimise noise exposure (Natus Mini Muffs, Natus Medical Inc., San Carlos, CA) and monitored by pulse oximetry, then wrapped and placed in an MRI-compatible incubator to keep the infant still, warm and supported in the scanner. Scanning will occur for about 45 to 60 min without sedation.The MRI protocol will include T1 turbo spin echo (TSE), T1w MPRage, T2w HASTE and 3 echo T2 map, 30 direction diffusion weighted imaging (DWI), and 64 direction DWI sequences. A neuroradiologist will review clinical sequences and classify any white and grey matter [58, 97] abnormalities. Diffusion images will be acquired using single-shot echo planar multi-direction diffusion-weighted sequence, employing dual bipolar diffusion gradient and double spin echo. This will include the acquisition of a 30 direction DWI protocol (b = 1000s/mm^2^) and a 64 direction HARDI protocol (b = 2000s /mm^2^), in which the encoding gradients are uniformly distributed in space (acquisition time 5 min and 11 min respectively). A field map for diffusion data is acquired using two 2D gradient recalled echo images to assist in correction for residual distortions due to susceptibility in homogeneities (acquisition time 1 min). An extensive pre-processing and quality control procedure will be used to detect and correct image artefacts caused by head movement, cardiac pulsation, and image distortions [60]. Fractional anisotropy (FA) and mean diffusivity (MD) will be estimated from corrected diffusion data using a diffusion tensor model. Constrained spherical deconvolution implemented in MRtrix will be employed to estimate fibre orientation distribution (FOD) [98]. Whole-brain voxel based analysis of FA and MD will be performed using tract-based spatial statistics optimised for neonates [99]. Whole-brain voxel-based analysis of fibre orientation distributions will be conducted using Apparent Fibre Density (AFD) [100]. Probabilistic tractography will be performed using MRtrix. White matter pathways will be delineated using the multi-regions-of-interest approach. A number of pathways, including corticospinal tract, corpus callosum, superior longitudinal fasciculus and thalamic radiations will be extracted. Summary measures of FA, MD, AFD and T2 within pathways will be calculated and related to EEG and clinical findings.iii.Preterm infant clinical measures8.Clinical assessments performed at baseline will also be performed at TEA; Prechtl’s Qualitative General Movements Assessment (GMA) [45] and Hammersmith Neonatal Neurological Examination (HNNE) [92]. All examinations will be performed by a Paediatric Neurologist, Paediatric Physiotherapist or Neonatologist blinded to allocation groups.A visual assessment will be performed at TEA. The Neonatal Vision Scale (NVS) [47] is a clinical assessment consisting of a short test battery that explores various aspects of visual function, ranging from the ability to fix and follow a target, to more complex aspects of visual function, such as reaction to a colour target, discrimination of black and white stripes with increasing spatial frequency and attention at a distance [47].The Bayley Scales of Infant and Toddler Development, Third Edition (Bayley-III) will be performed [48] at 24 months corrected age. Children will be assessed in the 5 key developmental domains of cognition, language, social-emotional, motor and adaptive behavior [48].The Infant Toddler Social and Emotional Assessment (ITSEA) will be measured at 24 months corrected age. The ITSEA is a 136-item parent report questionnaire to assess social and emotional problems and competencies in 4 domains of behavior: behavioural dysregulation; externalising behavior problems; internalising behavior problems and competencies [87].iv.Maternal measuresInfant Observation [85] performed at baseline will be repeated at TEA, 12 months and 24 months corrected age. This will be performed by the Psychoanalytic Psychotherapist who is blinded to randomisation.Questionnaires performed at baseline will also be performed at TEA; Depression Anxiety Stress Scales [79], Edinburgh Postnatal Depression Scale [95] and Mother-to-infant Bonding Assessment [96]. Mothers will be asked to complete these assessments.At 12 months corrected age, maternal infant responsiveness and maternal postnatal attachment will be measured. The MIRI, a 22-item scale [82] will be performed. The MPAS which has 19 items, all scored on a 5-point scale, with 1 and 5 indicating low and high attachment respectively, will also be performed [101]. Mothers will be asked to complete this assessment.At 24 months corrected age, the Maternal Self Efficacy Scale (MSES) will be measured. The MSES is a 20-item measure of the mothers’ perceived self-competence of their maternal practice used at 12 months. The measure has good internal consistency (Cronbach’s **α** = 0.76-0.89) and is a good predictor of maternal competence, with strong concurrent validity with observation [102]. Mothers will be asked to complete this assessment.

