### Data analysis

Summary statistics will be used to describe demographic and clinical data characteristics at baseline by allocated study treatment. Continuous data will be summarised using either mean and standard deviation, or median and inter-quartile range, depending on the distribution of the variable of interest. Categorical data will be presented as frequencies and percentages. Comparisons between the baseline values of the treatment groups will be conducted to assess the degree to which variables are comparable after randomisation. Between group differences will be investigated using linear regression for continuous data and Fisher’s exact test for categorical data. Potential confounding variables for the primary outcome are considered a-priori to be: gestational age at birth, birthweight, parity and maternal education. If any of these variables differ significantly between-groups (at *P* < 0.005), the identified variable(s) will be controlled for in the main analyses.

The primary study outcome is beta frequency global power measured in all VPT infants at term equivalent age. The mean difference between treatment groups will be calculated using linear regression with treatment group entered as the main effect. The corresponding 95 % Wald confidence interval and *p*-value will be reported. For secondary outcomes, we will present the effect estimate relating to a variable with a continuous outcome as a mean difference, which will be calculated using a linear regression model. If a continuous variable does not meet the assumptions necessary for linear regression, we will compare groups using the Mann–Whitney U Test. We will present the effect estimate relating to a variable with a binary outcome as an odds ratio, which will be calculated using a logistic regression model. We will present the effect estimate relating to a variable with a count outcome as an incident rate ratio, which will be calculated using a Poisson regression model. For all models the corresponding 95 % Wald confidence interval and p-value will be reported.

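### Infant Observation and DASS are repeated over follow-up, but the models named for secondary outcomes use no baseline value, visit term or within-pair correlation; one repeated-measures model would be a cheap gain

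*Protocol article*

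**What the plan says.** Under Baseline measures, the Infant Observation is introduced with a longitudinal purpose: "This will be the first of four such observations to evaluate the evolving mother-infant relationship". Under Secondary outcomes (maternal measures), it is "performed at baseline will be repeated at TEA, 12 months and 24 months corrected age". Table 1 agrees, and also places DASS at baseline, TEA and 24 months. These schedules are for preterm pairs; term-born pairs have two observations (Table 2).

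The Data analysis section then gives a method for each type of secondary variable. For continuous outcomes: "For secondary outcomes, we will present the effect estimate relating to a variable with a continuous outcome as a mean difference", from a linear regression, with the Mann–Whitney test if its assumptions fail. Binary outcomes get logistic regression and counts get Poisson regression. The section does not mention the baseline value of an outcome, a visit term, a group-by-visit term or correlation within a pair. The only covariates it names are gestational age at birth, birthweight, parity and maternal education, each used only if the groups differ on it at P < 0.005.

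The attachment hypothesis is a between-group statement: "Infant massage by the mother in VPT infants enhances infant attachment". The Aim says that maternal mood and anxiety and infant attachment "will be measured at term equivalent age, 12 months corrected and 24 months corrected age".

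**The concern.** The design and the named analysis do not match. The trial pays for a baseline and repeated follow-up on the same pairs, and for Infant Observation it says that the repeats are there to follow how the relationship develops. None of the named models links one visit to another.

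Three things are at stake, all for secondary outcomes:

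- **Precision.** With about 20 pairs per arm, ignoring a correlated baseline and the other follow-ups leaves each comparison able to detect only a large difference.
- **Persistence.** A difference at TEA and none at 24 months, tested separately, is not a test that the effect faded. That needs the contrast between visits with its own standard error.
- **Partial follow-up.** A pair seen at TEA and lost later enters the TEA regression but not a 24-month one. A joint model lets its earlier data inform the later estimate.

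If all visits were instead stacked in one ordinary regression, correlation within pairs would be ignored and the standard errors would be wrong.

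**Working it through.** **The plan's own figure.** The Sample size section asks for 20 completers per group with two thirds retained at TEA: 20 / (2/3) = 30 per group, 60 in total. This reproduces. The 20 itself cannot be checked, because no SD is given for the EEG outcome. It is used here only as the number of pairs per arm.

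**Inputs from the protocol.** 20 per arm (Sample size); two-sided alpha of 0.05 (Data analysis); 80% power (stated there for the EEG outcome, borrowed here); three post-baseline observations for Infant Observation and two for DASS (Table 1).

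**Assumptions not in the protocol.** A numeric score; the same correlation rho between any two visits (compound symmetry), taken as 0.3, 0.5 and 0.7; no loss after TEA; for the average over visits, a steady effect.

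**Step 1: one unadjusted visit.** The normal formula gives (1.960 + 0.842) × √(2/20) = 0.886 SD. The noncentral t with 38 degrees of freedom gives 0.909 SD, which is the reference below.

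**Step 2: variance of the group difference relative to one unadjusted visit.**

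- One visit with baseline as covariate: 1 − rho².
- Mean of k post-baseline visits with baseline as covariate: (1 + (k − 1)rho)/k − rho².
- Change in the group difference between two follow-ups, such as TEA to 24 months: 2(1 − rho). Under compound symmetry the baseline is uncorrelated with that change, so adjusting for it does not help.

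**Step 3: detectable difference = 0.909 × √(factor).**

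| Analysis | rho 0.3 | rho 0.5 | rho 0.7 |
|---|---|---|---|
| One visit, unadjusted | 0.91 | 0.91 | 0.91 |
| One visit, baseline-adjusted (factors 0.91, 0.75, 0.51) | 0.87 | 0.79 | 0.65 |
| Mean of three visits, baseline-adjusted (factors 0.443, 0.417, 0.31) | 0.61 | 0.59 | 0.51 |
| Mean of two visits, baseline-adjusted, as for DASS (factors 0.56, 0.50, 0.36) | 0.68 | 0.64 | 0.55 |
| Change in group difference between two follow-ups (factors 1.4, 1.0, 0.6) | 1.08 | 0.91 | 0.70 |

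Worked cell: at rho = 0.5 with three visits, (1 + 2 × 0.5)/3 − 0.25 = 0.417, and 0.909 × √0.417 = 0.587.

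**Step 4: the same in power.** For a steady 0.6 SD effect at rho = 0.5, power is about 46% for one unadjusted visit, 57% with baseline adjustment and 82% for the average of three visits.

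**Step 5: when the effect is not steady.** If a difference existed at TEA only, the three-visit average would be one third of it. Detecting an average of 0.587 SD would then need 3 × 0.587 = 1.76 SD at TEA, whereas a baseline-adjusted TEA comparison needs 0.79 SD. The average should therefore be reported beside the visit-specific differences and not replace them.

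**The case against.** The strongest reply is that the Data analysis section lists an effect measure by variable type and does not fix the occasion, the covariates or the way visits are combined. This is a condensed article, and the detail may sit in an analysis plan that is not shown. Much of this stands, and it rules out several stronger readings that a reader might infer:

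- *The plan requires a separate regression at each visit.* It does not say so. That is an inference from the models named.
- *The plan cannot examine evolution.* Too strong. A change score, a per-pair slope or a baseline-adjusted follow-up value could each be put into a linear regression and yield a mean difference. The text specifies none of these.
- *The trial's own question goes unanswered.* The stated hypothesis is a group effect on attachment, and visit-by-visit comparisons do address it, though less precisely. The phrase about the evolving relationship describes an instrument; it is not a declared estimand.
- *The repeated data are wasted.* Not shown. Each visit would still be used in its own comparison.

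It is also fair to say that the protocol gives Infant Observation only as a list of criteria, starting "Each observation will be assessed using the following criteria: amount of touching by the mother", with no score or scale. A single model cannot be prescribed for criteria that turn out to be purely descriptive, and the SD figures apply only where a numeric score exists.

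What survives is that the section is not silent. It states a model family for each outcome type and a closed list of possible covariates, and neither uses the baseline value or the repeated structure.

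**Conclusion.** The point holds as a cheap improvement confined to secondary outcomes. Applied as written, the named models give unlinked contrasts that are less precise than the design allows and provide no direct estimate of whether a difference persists or fades.

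For Infant Observation, the average post-baseline difference detectable with 80% power falls from 0.91 SD (one unadjusted visit) to about 0.61, 0.59 or 0.51 SD at rho 0.3, 0.5 or 0.7. Part of this comes from the baseline covariate alone, which gives 0.87, 0.79 or 0.65 SD at a single visit. These figures rest on compound symmetry, 20 pairs per arm at every visit, a numeric score and a steady effect. Only the 20 per arm comes from the protocol, and there it is tied to completion and TEA retention.

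A reader might take the 0.59 SD or the 82% power as the ability to detect a changing effect. They are not: both concern the average over visits. The group-by-visit contrast still needs about 0.91 SD at rho 0.5, so a joint model would estimate it directly but with little power. The primary EEG outcome, measured once at TEA, and the sample size are unaffected.

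**What to change.** Add to the Data analysis section that DASS (TEA and 24 months), and each Infant Observation criterion scored numerically or as a count (TEA, 12 and 24 months), will be analysed in one repeated-measures model:

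- a linear mixed model for numeric scores, or the corresponding model with a matching link for counts;
- group, visit and group-by-visit as fixed effects, with the baseline value of the same measure as covariate;
- the mother–infant pair as the clustering unit;
- a small-sample degrees-of-freedom correction.

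Report the group difference at each visit, the average post-baseline difference and the group-by-visit contrast, each with its confidence interval. State which Infant Observation criteria are scored, and on what scale.

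The cost is a few sentences of wording and slightly more analysis work. No visits, measurements or participants are added. The downside is a working covariance assumption.
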